## Abstract

**Background:**

Severe arthritis of the knee is a disabling condition, with over 50,000 knee replacements performed each year in the UK. Isolated patellofemoral joint arthritis occurs in over 10% of these patients with the treatment options being patellofemoral arthroplasty or total knee arthroplasty. Whilst many surgeons believe total knee arthroplasty is the 'gold standard' treatment for severe knee arthritis, patellofemoral arthroplasty has certain potential advantages. Primarily, because this operation allows the patient to keep the majority of their own knee joint; preserving bone-stock and the patients' own ligaments. Patellofemoral arthroplasty has also been recognised as a less 'invasive' operation than primary total knee arthroplasty, facilitating a more rapid recovery. There are currently no published results of randomised clinical trials comparing the two arthroplasty techniques. The primary objective of the current study is to assess whether there is a difference in functional knee scores and quality of life outcome assessments at one year post-operation between patellofemoral arthroplasty and total knee arthroplasty. The secondary objective is to assess the complication rates for both procedures.

**Methods/design:**

Patients who are deemed suitable, by an Orthopaedic Consultant, for patellofemoral arthroplasty and medically fit for surgery are eligible to take part in this trial. The consenting patients will be randomised in a 1:1 allocation to a total knee or patellofemoral arthroplasty. The randomisation sequence will be computer generated and administered by a central independent randomisation service. Following consent, all participants will have their knee function, quality of life and physical activity level assessed through questionnaires. The assigned surgery will then be performed using the preferred technique and implant of the operating surgeon. The first post-operative assessments will take place at six weeks, followed by further assessments at 3, 6 and 12 months. At each assessment time point all complications will be recorded. In addition, community and social care services usage will be collected using a patient questionnaire at 3, 6 & 12 months. The patients will then be sent an annual postal questionnaire. The questionnaire will ask about any problems, knee pain and function following their knee arthroplasty to monitor long-term function and failure rates.

**Discussion:**

This trial is expected to deliver results in early 2013.

**Trial Registration:**

ISRCTN: ISRCTN34863373

UKCRN portfolio ID 6847

## Background

### Isolated patellofemoral arthritis and treatment options

Severe arthritis of the knee is a common and disabling condition. Over 50,000 patients require a knee arthroplasty each year in the UK at an estimated cost of 300 million pounds. Arthritis confined to the patellofemoral joint (the articulation between the patella and the trochlear groove of the femur) occurs in over 10% of these patients. The average age of those affected by isolated arthritis of the patellofemoral joint is significantly lower than those with severe generalised arthritis [1]. Commonly, patients complain of anterior knee pain which limits their daily activities and in severe cases patients are unable to continue in employment. Initially, these symptoms can be successfully treated non-operatively. However, in severe debilitating cases the efficacy of these non-surgical modalities is minimal and the only alternative treatment is surgery. The operative treatment options for this disease include arthroscopic procedures, patellectomy (removal of the knee-cap), Total Knee Arthroplasty (TKA) and more recently, Patellofemoral Arthroplasty (PFA). Arthroscopic surgery is seldom beneficial in severe disease and patellectomy often leads to poor long-term function, therefore the choice for patients is usually between TKA and PFA.

Whilst many surgeons believe TKA is the 'gold standard' treatment for severe knee arthritis, PFA has certain potential advantages. Primarily, this operation allows the patient to keep the majority of their own knee joint; preserving bone-stock and the patients' own ligaments. PFA has also been recognised as a less 'invasive' operation than TKA, facilitating a more rapid recovery [2]. Despite these perceived advantages, early PFA designs yielded less than satisfactory results due to residual patella mal-alignment, wear of polyethylene and failure secondary to disease progression in the other parts of the joint [3]. More recent studies, however, have shown significantly better results with PFA. This is due to improved implants, an appreciation of the need to balance the soft tissues and more appropriate patient selection when considering PFA [4].

In a retrospective case series study, Cartier et al. [5] reported excellent functional outcome in 77% of patients at a mean of 10 years follow-up. These findings substantiate those of an earlier retrospective consecutive case study, where good or excellent functional results were reported, using the Knee Society Score (KSS), in 86% of 'residual' cases at 17 years [6]. Most recently, Odumenya et al. [7] and Stark et al [8] have reported excellent functional outcomes with 100% survivorship at 5 and 2 years follow-up, respectively. Therefore, there is some evidence to suggest that PFA provides positive results for patients with isolated patellofemoral arthritis. It is however not clear how the latest generation of PFA compare with the excellent long-term results of Total Knee Arthroplasty [9]. The majority of the remaining literature consists of case series with short-term results and includes only a small number of studies on the use of TKA for primarily severe patellofemoral arthritis. Mont et al. [10] reported 97% good or excellent clinical results using the KSS at a mean follow-up of over 6 years. These results are in agreement with the findings of Laskin et al. [11] who reported on forty-two patients managed with TKA for primary patellofemoral arthritis. This study compared the use of TKA in patients with patellofemoral arthritis and tricompartmental arthritis. They concluded that the results of TKA in the patellofemoral subgroup were superior to those patients with tricompartmental arthritis. However, these inferences are uninformative when deciding between TKA and PFA for the treatment of isolated patellofemoral arthritis.

There are currently no published results of randomised clinical trials comparing the two arthroplasty techniques. At present the only registered study (ISRCTN22478626) directly comparing TKA and PFA was not performed. We therefore propose the first trial comparing TKA with PFA to provide surgeons and patients with accurate information regarding knee function. The null hypothesis for this trial is that there is no difference in functional score (WOMAC - Western Ontario and McMaster Universities Osteoarthritis Index score) at one year post-operation between Total Knee Arthroplasty and Patellofemoral Arthroplasty.

## Methods/Design

### Design

This is a two-arm, double-blind, randomised clinical trial performed in a single centre (University Hospitals Coventry and Warwickshire NHS Trust) in the United Kingdom. The participant and assessor (research associate) are both blinded to the treatment allocation throughout the entire study. This study has been reviewed by the Coventry Research Ethics Committee under reference number 09/H1210/9. The study was approved on the 3^rd ^of March 2009. The research carried out is in compliance with the Helsinki Declaration.

### Study participants

#### Inclusion criteria

The eligibility criteria for participation in this study is that the patient is medically fit for an operation and has severe isolated patellofemoral osteoarthritis of the knee deemed suitable for a patellofemoral arthroplasty by the responsible consultant orthopaedic surgeon. It is accepted that all patients deemed suitable for PFA are also suitable for TKA. These broad eligibility criteria should ensure that the results of the study can readily be generalised to the wider population of patients with severe isolated patellofemoral osteoarthritis.

#### Exclusion criteria

Contra-indications to surgery include patients with tibiofemoral osteoarthritis of the knee and those unfit for surgery, defined as: (i) severe cardiac impairment, e.g. heart or valve replacement, arrhythmia, previous myocardial infarction, (ii) severe respiratory impairment, e.g. chronic obstructive pulmonary disease, asthma that has required hospital admission, or (iii) any other systemic medical condition that would produce a specific contraindication to a general anaesthetic. There is no fixed age range.

In addition, patients who are unable to adhere to trial procedures or complete questionnaires, for reasons such as dementia or intravenous drug use, will be excluded.

If a recruited patient requires contra-lateral knee arthroplasty surgery during the trial period, this second knee will not be included in the study (i.e. it will not be randomised) since the result of this intervention would not be independent of the first intervention.

#### Recruitment

Patients will be recruited from orthopaedic clinics at University Hospitals Coventry and Warwickshire NHS Trust. Upon identification of an eligible patient by the orthopaedic consultant, the patient will be referred to the research associate present in the clinic. The research associate will provide the patient with the patient information sheet and verbally explain what the trial entails. The patient will then be given the opportunity to discuss any issues with the research associate, their consultant as well as members of their family and friends.

#### Consent

Informed consent will be obtained by the research associate, after allowing sufficient time for the patient to consider their decision and ask questions about the trial. Any new information that arises during the trial that may affect participants' willingness to take part will be reviewed by the Trial Steering Committee, and, if necessary, communicated to all participants by the trial coordinator.

If the participant decides to withdraw, their care will continue as normal for the hospital. If the participant decides to continue in the study they will be asked sign an updated consent form.

#### Post randomisation withdrawals

Patients may withdraw from the trial at any time without discrimination. If patients decide to have the treatment to which they were not randomised, they will be followed-up where feasible and data collected as per the protocol until completion of the trial. The primary analysis will be on an intention-to-treat basis with a secondary per-protocol analysis. If patients have neither treatment during the course of the trial, they will be followed up in the same way as the other patients in the trial and included in the intention-to-treat analysis.

### The Study Intervention

The two treatments in this study are patellofemoral arthroplasty and total knee arthroplasty. In this pragmatic trial, each patient will undergo the allocated surgery according to the preferred technique and preferred implants of the operating surgeon.

In summary, the details of the surgery will be left entirely to the discretion of the surgeon to ensure that the results of the trial can be generalised to as wide a group of patients and surgeons as possible.

#### Patellofemoral Arthroplasty

Patellofemoral joint arthroplasty involves replacement of the articular surfaces of the femoral trochlear groove with a contoured metal implant and, usually, the under-surface of the patella with a plastic 'button'. Both articulating areas are resected using jigs and clamps respectively. The implants are then cemented in place using bone cement (see Figure 1). The native tibiofemoral joint remains in situ.

**Figure 1 F1:**
[figure not shown]
**AP radiograph showing a Patellofemoral Arthroplasty**.

#### Total Knee Arthroplasty

In total knee arthroplasty, the tibiofemoral articulation is also replaced. The top of the tibia is resurfaced with a flat metal plate with a plastic 'spacer' on top. The upper part of the knee joint, the femoral condylar articulating surface, is replaced with a contoured metal implant that fits around it and includes the trochlear groove. The patella is usually resurfaced with a plastic button similar to that used in the PFA. All the implants are cemented to bone (see Figure 2).

**Figure 2 F2:**
[figure not shown]
**AP radiograph showing a Total Knee Arthroplasty**.

#### Rehabilitation

The same standard rehabilitation program will be implemented for all patients, as outlined in the University Hospitals Coventry and Warwickshire NHS Trust 'Knee Replacement: A Guide for Patients' booklet. This includes early exercises, precautions to be followed for the first three months, how to perform functional activities and advanced exercises.

#### Follow-up

Patients will continue in routine clinical follow-up, according to their surgeon's practice. For this trial, the primary outcome point will be at one year, with other scheduled assessments at 6 weeks, 3 months and 6 months post operation. At all these assessment time points patients will come to the clinic to be reviewed by the research associate, and if necessary an orthopaedic surgeon. Thereafter, an annual postal questionnaire will be sent to each patient including the Oxford Knee Score, Euroqol and an additional treatment questionnaire to monitor long term function and failure rates.

In this study, we will use techniques common in long term cohort studies to ensure minimum loss to follow-up, such as collection of multiple contact addresses and telephone numbers, mobile telephone numbers and email addresses. Considerable efforts will be made by the trial team to keep in touch with patients. Using these techniques, with only 64 participants to track, we are confident that loss will not exceed 10%. In the event of a participant being lost to one year follow-up, we will consider, on the advice of the trial statistician, imputing missing primary outcome data from interim scores.

A system of reminders will be instituted to ensure that return to clinic at three, six and twelve months is as complete as possible. The research associate will phone participants to make an appointment and after two weeks non-response a letter will be sent out to the patient. The letter will be followed up by phone call after 1-2 weeks. If there is no response from participant, they will be classified as a 'non-responder'.

### Study objectives

There are two main objectives of this randomised clinical trial:

1. To quantify and draw inferences on observed differences in primary and secondary outcomes measures between the trial treatment groups at one year post-operation.

2. To determine the complication rate of Patellofemoral Arthroplasty versus Total Knee Arthroplasty at one year post-operation.

### Outcome measures

The primary outcome measure is: ***WOMAC (Western Ontario and McMaster Universities) Osteoarthritis Index score***. This is a validated questionnaire, which is self-administered (filled out by the patient). It consists of 24 items (5 for pain, 2 for stiffness and 17 for physical function), all related to daily tasks, which are directly influenced by poor function resulting from osteoarthritis. The minimum (best) score attainable is 0 and the maximum (worst) score is 96 [12].

Five secondary outcome measures will be used in this trial: (i) ***Oxford Knee Score (OKS)***: This is a self-administered, validated knee arthroplasty functional outcome measure consisting of 12 items related to daily activities. The score ranges from 12 to 60, where 12 represents the best outcome and 60 represents the worst outcome [13]., (ii) ***American Knee Society Score (AKSS)***: This is also a validated knee function questionnaire, which is divided into two sections: knee score and function score. The knee score is comprised of assessments of range of motion, stability, alignment, and muscle power of the knee. The function score includes an assessment of daily tasks to determine functional ability. Both scores range from 0 to 100 points (100 points being the best score). The research associate fills out this questionnaire [14], (iii) ***Euroqol (EQ-5D)***: This validated quality of life (QoL) questionnaire consists of 5 domains related to daily activities, each with a 3-level answer possibility. The combination of answers leads to the QoL score. The patient completes this form [15], (iv) ***Disability Rating Index***: a self-administered, 12-item Visual Analogue Score (VAS) questionnaire assessing the patient's own rating of disability [16], (v) ***UCLA Physical Activity Questionnaire***: The University of California Los Angeles activity-level rating is a self-rating scale from level 0-complete inactivity to level 10- participation in impact sports [17]. All complications will be recorded throughout the duration of the trial.

### Sample size

Previous work has suggested that the WOMAC score is the most sensitive condition-specific tool for assessing interventions in knee osteoarthritis [12,18]. Angst et al. [19] successfully demonstrated the use of the 17-item functional section of the WOMAC score to determine sample size.

The sample size calculation was based on a two-arm parallel group design and an assumed approximate normal distribution for the primary outcome measure (WOMAC). The required number of patients in each arm of the trial is 29, based on an independent samples *t*-test and an assumed population standard deviation of 10.8 points [20] and a minimum clinically important difference of 8 points [19]; this gives a relatively large standard effect size of 0.74. The proposed number of patients will provide 80% power to detect a difference at the 5% level (PS, Power and Sample Size Calculation Software version 2.1 30th February 2003, available at http://biostat.mc.vanderbilt.edu/wiki/Main/PowerSampleSize). To allow for a 10% loss to follow-up we will aim to recruit 32 patients in each arm, giving a total of 64 patients.

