### Statistical analysis

Standard statistical summaries (e.g. medians and ranges or means and variances, dependent on the assumed distribution of the outcomes) and graphical plots showing correlations will be presented for the primary outcome measure (WOMAC) and the secondary outcome measures. Baseline data will be summarized to check comparability between treatment arms, and to highlight any characteristic differences between those individuals in the study, those ineligible, and those eligible but withholding consent. The main analysis will investigate differences in the primary outcome measure, the WOMAC score, between the two treatment groups on an intention-to-treat basis at 12 months post-operation. The significance in responses between treatment groups will be formally assessed using an independent samples *t*-test; based on an assumed approximate normal distribution for this outcome measure. Tests will be two-sided and considered to provide evidence for a significant difference if p-values are less than 0.05 (5% significance level). Estimates of treatment effects will be presented with 95% confidence intervals. A linear regression analysis will also be undertaken that will incorporate terms that model the effects of patient age and gender in addition to the effects of the treatment groups (TKA and PFA). Results from the unadjusted and adjusted analyses will be presented graphically, together with diagnostic plots that check the underlying model assumptions. Depending on the nature of the data, various derived variables (e.g. logarithmic transformations of scores) may be created and analysed, in addition to the primary outcome. Although missing data is not expected to be a problem for this study, the nature and pattern of the missingness will be carefully considered -- including in particular whether data can be treated as missing completely at random (MCAR). If judged appropriate, missing data will be imputed, probably using the multiple imputation facilities available in R http://www.r-project.org/. A detailed statistical analysis plan (SAP) will be agreed with the Data Management Committee (DMC) at the start of the study. Any subsequent amendments to this initial SAP will be clearly stated and justified. Interim analyses will be performed only where directed by the DMC. The routine statistical analysis will be carried out using R http://www.r-project.org/.

This trial is expected to deliver results in early 2013.

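### 29 per arm gives about 79% power, not 80%, for the two-sided t-test the protocol names, and the allowance for 10% loss leaves no margin to absorb the gap

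*Protocol article*

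**What the plan says.** The Sample size section of the protocol article bases the calculation on an independent-samples t-test with "an assumed population standard deviation of 10.8 points" and "a minimum clinically important difference of 8 points", and adds that "this gives a relatively large standard effect size of 0.74". From these it concludes: "The required number of patients in each arm of the trial is 29". On power it says: "The proposed number of patients will provide 80% power to detect a difference at the 5% level". The step from evaluable to recruited patients is: "To allow for a 10% loss to follow-up we will aim to recruit 32 patients in each arm, giving a total of 64 patients".

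The Statistical analysis section confirms the test. The 12-month WOMAC comparison is to be "formally assessed using an independent samples *t*-test", two-sided, with significance declared below 0.05.

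The Follow-up section treats 10% as a ceiling on losses among the 64 participants.

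**The concern.** The protocol ties a power figure to a named test and gives every input, so the figure can be checked. For that test, 29 per arm falls just short of 80%. An allowance for loss with some slack would cover so small a gap, but 32 per arm less 10% returns to 29 at best. The claim of 80% power after the allowed loss is therefore not met on the protocol's own inputs. What is at stake is the accuracy of a stated design figure that readers will carry into the trial report; no decision on design or analysis depends on it.

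**Working it through.** **Inputs.** SD 10.8, difference 8, 80% power, 5% level, 29 per arm, and 32 per arm (64 in total) after 10% loss, all from Sample size. Two-sided independent-samples t-test, from Statistical analysis. 1:1 allocation, from Randomisation. Loss of at most 10% of 64, from Follow-up.

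**Effect size.** 8 / 10.8 = 0.7407, which agrees with the stated 0.74.

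**Reproducing 29.** The normal approximation is n per arm = 2 × (z for 0.975 + z for 0.80)² × (SD / difference)² = 2 × (1.960 + 0.842)² × (10.8 / 8)² = 28.61, rounded up to 29. The stated figure is matched by this formula.

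**The named test.** Exact power uses the noncentral t distribution with 2n − 2 degrees of freedom and noncentrality 0.7407 × √(n/2). At n = 29 the degrees of freedom are 56, the critical value is 2.003 and the noncentrality is 0.7407 × √14.5 = 2.821. Power by number evaluable per arm:

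| Evaluable per arm | t-test power |
|---|---|
| 28 | 77.7% |
| 28.8 | 78.9% |
| 29 | 79.2% |
| 30 | 80.5% |
| 32 (no loss) | 83.1% |

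Solving for exactly 80% gives n = 29.60, so 30 per arm. With 29 per arm, the difference detectable with 80% power is 8.09 points.

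**The allowance for loss.**
- On average: 32 × 0.90 = 28.8 per arm, with 78.9% power.
- In whole patients: 10% of 64 is 6.4, so at most 6 may be lost (7 would be 7/64 = 10.9%). That leaves 58, or 29 per arm if losses are even, with 79.2% power. An uneven 28/30 split gives 79.1%.
- Dividing strictly by the retained fraction: 29 / 0.90 = 32.2, which rounds up to 33, one more per arm than the target.
- The 80% mark is passed at 30 per arm, that is 60 of 64 retained: 4 lost, evenly split, or 4/64 = 6.25%. It is reached with losses somewhat below the allowance, but not at the allowance itself.

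**The case against.** The strongest reply is that this is one patient per arm and about one percentage point of power, far inside the uncertainty of an assumed SD of 10.8. On the normal approximation, which reproduces 29, even 28.8 per arm has 80.3% power. Both statements are true, and they fix the size of the point. They do not remove it, because the protocol names the t-test both for the sample size and for the analysis.

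A reader might infer more than the document supports, in four ways.

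- *That the loss allowance takes the trial below its required 58.* It does so only in fractions of a patient (64 × 0.90 = 57.6). Counted in whole patients under the stated ceiling, 58 remain. Power falls more than two points short only with 28 in both arms, meaning 8 of 64 lost (12.5%), which is beyond what the protocol allows.
- *That 29 is known to come from the normal formula, and 32 from multiplying by 1.10.* Both fit (29 × 1.10 = 31.9). But a t-based 29.6 cut down to 29, and 32.2 rounded to the nearest whole number, fit as well. The protocol names its software and shows no formula.
- *That the gap leaves the trial without reserve for patients who switch or receive neither operation.* That does not follow from a rounding gap. An exact calculation allowing only for 10% loss would provide no such reserve either.
- *That adjusting for baseline would restore 80%.* This needs a correlation between baseline and 12-month scores, which the document does not give. The planned regression names age and gender.

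**Conclusion.** The point holds at rounding level. For the two-sided 5% t-test with SD 10.8 and a difference of 8, the requirement is 30 per arm rather than 29. With the full 10% loss, 64 recruited gives 78.9% to 79.2% power. The difference from the claim is about one percentage point, and it runs against the plan because the recruitment target has no slack. The claim that the trial is materially underpowered is not supported: the stated sizes are right to within one patient per arm before loss, and power is 83.1% if nobody is lost. The conclusion takes the protocol's SD, difference and loss ceiling as given, with roughly even losses between arms. It is a minor correction.

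**What to change.** Keep the target of 64 and restate the power in the Sample size section, for example: *64 recruited, about 58 evaluable after up to 10% loss, gives about 79% power by two-sided t-test to detect 8 points with SD 10.8.* The required number should then no longer be presented as giving 80% for the t-test.

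The cost is one sentence and a slightly less favourable stated power. No extra patients and no change to the analysis are needed.
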